## Abstract

**Background:**

Osteopathic medicine is based on a diagnostic and therapeutic system to treat tissue mobility/ motility dysfunctions in general, using different approaches (depending on the target tissue) known as osteopathic manipulative treatment. Among the available techniques those ones addressed to the cranial field are the most questioned because of the lack of scientific evidence; but the compression of the 4th ventricle technique has been largely studied in clinical trials. Studies have shown that the technique may affect both central and autonomous nervous system, modulating some reflexes (Traube-Hering baro signal), and modifying brain cortex electrical activity through central sensitization in subjects with chronic low back pain. Thus, investigators hypothesize that the compression of the 4th ventricle may modulate peak alpha frequency (eletroencephalographic assessment) and promote physical relaxation in subjects in vigil.

**Methods/Design:**

A randomized, controlled crossover trial with blinded assessor was designed to test the hypothesis. A total of 81 participants will be assigned to three treatment conditions, with seven days of washout: (I) compression of the 4th ventricle; (II) sham compression of the fourth ventricle; (III) control (no intervention). The (I) power amplitude and the (II) frequencies of the dominant peak in the alpha band will be the primary outcome measures of the study. All participants will be recruited at the Outpatient Rehabilitation Service of the University Hospital of Brasília – University of Brasília. All the electroencephalographic exams will be conducted by a blinded assessor.

**Discussion:**

The investigators hypothesize that patients with chronic low back pain submitted to the technique would have the peak alpha frequency modulated and, thus, would experience physical relaxation.

**Trial registration:**

NCT02111382

## Background

Osteopathic Medicine (OM) is based on a diagnostic and therapeutical system to treat tissue mobility dysfunctions in general [1]. The Osteopathic Manipulative Treatment (OMT) uses different techniques according to the dysfunctional tissues. The World Health Organization considers OM as complementary or alternative medicine, and it is based on concepts and unique approaches that enable the self-healing and self-regulating process within the body [2, 3]. This increasing interest in osteopathic medicine may reflect the reality of the society because patients turn to complementary or alternative treatments whereas the conventional treatments seem to fail in producing the desired outcome, or to produce side effects [4]. In the United States, the overall expenditure for complementary and alternative medicine is in the tens of billions of dollars per year [4].

Among the available OMT techniques, those addressed to the cranial field are the most questioned because of the lack of scientific evidence. A systematic review of 7 randomized controlled trials revealed studies heterogeneity, studies with poor methodology and not enough data to draw a conclusion about Osteopathy in the Cranial Field (OCF). One of the keystones of OCF teaching and practice is the presence of Primary Respiratory Mechanism (PRM) – which is partially represented by the movement of the cranial bones [5]. So, much discussion remains on the hands ability to perceive PRM through the obliterated sutures of the skull in adults, besides the lack of evidence to support them [6, 7].

One of the most studied OCF techniques is the Compression of the 4th Ventricle (CV4) - the osteopath exerts a compression force on the lateral angles of the squama occipitalis. The CV4 technique affects both central and autonomous nervous system [8], assessed by change in the blood flow and in the tissue oxygen saturation [9, 10]. Another way to measure the effects of the CV4 technique is the brain cortex electrical activity by electroencephalography (EEG), which is a validated method to support the results [11–14]. Current literature has only 2 crossover studies with healthy participants: the work of Cutler et al. [15] showed a decrease in sleep latency; and Miana et al. [16] showed an increase in the absolute power of alpha frequency. The EEG exam is useful to detect changes in the central processing of pain [17] and in patients with chronic pain, one study showed increased power amplitude in alpha frequency bands and a shift towards lower frequencies of the dominant peak [18]. These outcomes are important to develop new trials on diagnosis and therapeutics because of the increasing number of subjects with chronic pain in world [19, 20].

Therefore, this study aims to assess brain cortex electrical activity (alpha band frequency) in individuals with nonspecific chronic low back pain submitted to CV4 technique. The investigators hypothesize that patients with chronic low back pain submitted to the technique would have the peak alpha frequency (PAF) modulated and, thus, would experience physical relaxation.

## Methods and design

### Design and setting

This is a randomized, controlled crossover trial.

The participants will be recruited from the outpatient rehabilitation service of the University Hospital of Brasília from August 2015 to August 2017 through the media (daily papers, local newspapers, and public newsletters) at the hospital, and on the University of Brasilia website. The eligible participants will be randomly allocated in the three groups of study with seven days of washout. The participants will be given a written consent form before the start of the study, and they also will verbally consent the trial. Figure 1 summarizes the study planning.

**Fig. 1 Fig1:**
[figure not shown]
Trial flow chart showing cross-over design and assessment points

The participants will be instructed to keep their sleeping and eating habits, as well as their daily living activities. They also will be advised not seek any other therapies, like massaging, physiotherapy, stretching and yoga to prevent any intervening factors during the trial period.

### Inclusion criteria

Participants over 18 years old with self-reported chronic low back pain will be recruited from the University Hospital of Brasilia. To ensure the inclusion criteria, an orthopedic physician will do the assessments all individuals who has interested in the study. Participants with chronic, recurrent, or long-lasting pain on musculoskeletal system for at least 6 months will meet the definition of chronic low back pain and, so, will be eligible to the study. To inclusion in the study the participants needs to presents: (I) a primary back pain form (i.e. progressive degenerative joint disease that result in biomechanical stresses affecting articular and extra-articular tissue) diagnosed by the physician according clinical and radiological findings; (II) only low back pain, to the Quebec Task Force [21]; and (III) absence of mental impairment determined by obtaining a score of 27 on the Mini Mental State Examination (MMSE) [22].

### Exclusion criteria

Participants suffering wiil be excluded if they present: (I) secondary chronic low back pain (ankylosing spondylitis, infections, malignancy, nephrolithiasis, pyelonephritis, aortic aneurysm, disease of the pelvic organs and gastrointestinal tract); (II) fever, chills, sweating, relate of weight loss superior of 5 % in the last 2 months without a clear cause, asthenia, anorexia; (III) cardiovascular and respiratory symptoms such as chest pain, dyspnea and cough; (IV) headache, dizziness, lightheadedness, fainting, tremors, dysarthria and aphasia; (V) surgery on the spine; (VI) diagnosis of any neurological, cardiac, respiratory and rheumatic disease; (VII) regular use of drugs with effects on the central nervous system (stimulants or depressors of CNS, examples: anxiolytics, anti-depressives, neuromodulators, etc.); (VIII) previous manual therapy treatment before data collection (in a four-eight weeks period of time); (IX) signs of nerve root involviment.

### Participants randomization and allocation

After participants selection, randomization will be performed using a computerized random number generator through the stratified simple randomization method of a software program (Excel, Microsoft Office 2008) for sequence generation. Sequentially numbered, opaque, sealed assignment envelopes will be delivered at the Hospital and the researcher will open one envelope in front of the participant; each envelope contains a concealed allocation number.

The three researchers performing the interventions will not have access to the order of allocation file. The allocation electronic file will be password-protected and only the fourth researcher will have the password to access it (ST).

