### Intervention

All participants will receive three interventions at the Outpatient Rehabilitation Service of the University Hospital of Brasília (room F49, blue hall), respecting a 7-days washout interval and the same appointment time, which may be scheduled between 8 and 11 a.m.

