### Statistical analysis and sample size

#### Baseline and outcome data

The baseline characteristics will be shown as the mean ± SD for continuous data (i.e., participant’s age and duration of back pain), and n (%) for categorical data (i.e., gender). To analyze the baseline characteristics, we will perform a One Way analysis of variance, or a Kruskal-Wallis test for continuous data if the data are normally distributed. Shapiro-Wilk test will be used to test data normality. The primary and secondary (EEG and pain) outcomes will be analyzed by 3 × 2 mixed-effects model (group [CV4 - CV 4 sham - Control] x time [pre and post]) to repeated data measures for each continuous outcome variable, we will also assesses if the allocation order will interfere in results, for thus we’ll analyze the order of allocation of CV4 (1^st^, 2^nd^ or 3^rd^) x pre values (CV4 – CV4 sham – Control) at the 3^rd^ exposition, using a one-way Anova or Kruskal-Wallis test. When the analysis of variance indicates significant differences among groups, a post-hoc test (Bonferroni test) will be used to separate the differences between groups before and after the intervention period. Data will be analyzed using Prism 6 software for Mac OS X, and a significance level of *p* ≤ 0,05 will be considered to all variables.

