#### Sample size

The sample size was calculated considering: (1) the two-way analysis of variance (ANOVA); [26] three groups; (3) type I error = 5 % (2-sided); (4) type II error = 20 %; (5) the power of the statistical test = 80 %; and (6) effect size = 20 %. The effect size was obtained considering: (I) the results from the pilot study of Miana et al. [16], which demonstrated a effect of 26 % (pre to post intervention) in the group that received the CV4 technique and (II) Cohen’s *d* which considers 20 % a small effect to calculate sample size and power analysis [27, 28]. Then, it was determined a total of 81 subjects. This calculation was performed in G Power 3 program, version for Mac OS X.

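### Condition order is randomised without restriction and the outcome model has no visit term, which costs precision if the pre-to-post response changes over the three visits

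*Protocol article*

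**What the plan says.** Under Participants randomization and allocation, the sequence is produced in Excel "through the stratified simple randomization method of a software program". No stratification factor, block or list of orders is given. Numbered envelopes are opened one per participant, and "each envelope contains a concealed allocation number".

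Design and setting describes the allocation as being to groups: "The eligible participants will be randomly allocated in the three groups of study with seven days of washout". The Intervention section makes clear that the design is a full crossover: "All participants will receive three interventions". What is randomised must therefore be the order of the three conditions.

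Under Baseline and outcome data, EEG and pain are analysed by a "3 × 2 mixed-effects model (group [CV4 - CV 4 sham - Control] x time [pre and post" structure. Visit number is not among the named factors. Order is examined separately ("we’ll analyze the order of allocation of CV4 (1^st^, 2^nd^ or 3^rd") by comparing pre-intervention values at the third exposure in a one-way analysis.

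**The concern.** Simple randomisation is a series of independent draws. Stratifying it without blocking or another restriction leaves each stratum a series of independent draws, so the order of conditions is not controlled whether or not strata exist. In a three-visit crossover, an effect of visit on the outcome can be dealt with in two ways: balance the orders across visits, or put visit in the model. The article's stated method does neither.

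The planned order check does not fill the gap. It looks at pre-intervention levels at the third visit by position of CV4. It neither estimates nor removes a visit effect on the pre-to-post change, which is the quantity compared between conditions.

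At stake is the precision of CV4 versus sham. If the response to a session weakens or strengthens with repetition (for example, through habituation), that variation enters the error term, and a chance imbalance of orders moves the estimate.

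**Working it through.** **The plan's own figure.** The Sample size section gives 81 subjects, with "type I error = 5 % (2-sided"), power of 80% and an effect size of 20%. Read as Cohen's f = 0.20 in a fixed-effects ANOVA with 2 numerator df, noncentral-F power reaches 0.80 at 244 observations: 244/3 = 81.3 per condition. Power at 81 × 3 = 243 observations is 0.798. So 81 reproduces, and nothing below changes it.

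**Inputs.**
- From the article: 81 participants, three conditions, three visits.
- Assumed: all 3! = 6 orders equally likely (the text lists none, and Figure 1 is not shown).
- Scale: the SD of the paired CV4-sham difference in change is 1 when there is no visit trend.
- Assumed: a linear visit trend in the change of 0 to 0.5 SD per visit. The total swing over three visits is twice the trend per visit, so 0 to 1 SD. The article gives no figure for this.

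**What cancels.** Both outcomes are measured before and immediately after each session. A shift in level at one visit affects pre and post alike and drops out of their difference. Only a trend in the change is left.

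**Imbalance under simple randomisation.**
- Six orders, 13.5 expected in each: median smallest 9, median largest 18.
- CV4 at a given visit: mean 27, SD = sqrt(81 × 1/3 × 2/3) = 4.24.
- Visit of CV4 minus visit of sham takes the values -2, -1, -1, 1, 1, 2 over the six orders. The mean is 0 and the variance is (4+1+1+1+1+4)/6 = 2. The SD of the mean gap is sqrt(2/81) = 0.157 visits, with a 95% range of 1.96 × 0.157 = ±0.31.
- A three-order Latin square gives gaps of -1, 2, -1 and the same variance, (1+4+1)/3 = 2. The 0.157 therefore does not depend on there being six orders; the 9 and 18 do.

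**Conditional shift in CV4 minus sham.** Trend per visit × gap: 0 at no trend; 0.2 × 0.31 = ±0.06 SD; 0.5 × 0.31 = ±0.15 SD. The standard error without a trend is 1/sqrt(81) = 0.11 SD.

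**Noise.** With no visit term, the paired difference has variance 1 + 2 × (trend per visit)².
- Swing 0.5 (0.25 per visit): sqrt(1.125/81) = 0.118. Simulated: 0.120.
- Swing 1 (0.5 per visit): sqrt(1.5/81) = 0.136. Simulated: 0.135.

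**Type I error and power.** Each setting had 10,000 simulated trials of the paired CV4-sham contrast. Power is taken at a true difference of 0.315 SD, chosen because it gives 80% power at 81 with no trend.

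| Swing (SD) | Orders | Type I error, no visit term | Power, no visit term | Power, visit term |
|---|---|---|---|---|
| 0 | simple | 0.053 | 0.798 | 0.787 |
| 0 | blocked | 0.047 | 0.801 | 0.801 |
| 0.5 | simple | 0.052 | 0.749 | 0.784 |
| 0.5 | blocked | 0.038 | 0.763 | 0.799 |
| 1 | simple | 0.049 | 0.629 | 0.795 |
| 1 | blocked | 0.017 | 0.648 | 0.801 |

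Blocking cuts the SD of the chance shift from 7.8% to 1.2% of the swing. Without a visit term, however, the test still counts the trend as error, so blocking alone makes it conservative and recovers little power. With a visit term, simple randomisation raises the variance of a contrast by only 1.3% on average over perfect balance (95th percentile 3.9%).

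**The case against.** The strongest reply is that each visit has its own baseline, so the familiar crossover worry about drift between visits is mostly met by design. That stands. A reader might infer that a pain trend, or EEG levels settling over the visits, would leak into CV4 versus sham. The measurement and analysis sections do not support this, because level shifts largely cancel in the pre-to-post change.

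A reader might also infer bias or false positives. Neither follows. The imbalance is by chance, the estimate is right on average, and type I error under simple randomisation stayed at 0.049 to 0.053. The shift is conditional on the orders drawn, and it is zero if the change has no visit trend. Nothing in the article shows that there is such a trend.

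Two further points stand. The article condenses a fuller protocol that may name strata and orders, so the text does not show that no strata exist. The planned order check also tolerates unequal groups: sizes of 20, 27 and 34 have a harmonic mean of 25.8 against 27, a loss below 5%.

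What the reply does not remove is that the stated method leaves the orders unrestricted under any strata, and that the model's named factors omit visit.

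**Conclusion.** The point holds as a matter of precision, at minor to moderate severity. The stated randomisation does not balance the order of conditions, and the stated model does not remove a visit effect on the change. If there is such an effect, the analysis loses power: negligibly at a swing of 0.25 SD (0.788), to about 0.75 at 0.5 SD and to 0.63 at 1 SD. For a given draw of orders, the shift in CV4 minus sham could reach ±0.15 SD at the top of the assumed range, somewhat more than one standard error of 0.11.

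These sizes rest on an assumed linear trend, on equally likely orders and on a paired-difference SD set to 1. It would be tempting to conclude that a blocked list by itself protects the comparison. The calculations do not support that: the visit term does most of the work, and blocking is a useful addition to it.

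**What to change.** **Main change.** In Baseline and outcome data, add visit number (1, 2, 3) as a factor in the outcome model. If the model is fitted to the change, a main effect is enough and spends two degrees of freedom. If it is fitted to pre and post values as separate rows, include visit by time as well, because a visit main effect alone absorbs only level shifts. On the change, the visit term restores power to about 0.78-0.80 under either randomisation scheme.

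**Secondary change.** In Participants randomization and allocation, replace the stratified simple wording with a statement that the orders, listed by name, are allocated in concealed permuted blocks of varying size. Either name the stratification factor or delete the word. In Design and setting, say that participants are allocated to orders, not groups. With six orders, 81 participants give about 13 or 14 per order; exact balance would need 78 or 84. Three Latin-square orders would divide 81 exactly (27 each) but would not balance first-order carryover.

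**Cost.** A new list before the envelopes are filled, and one addition to the model; no extra participants. The last orders in a block become partly predictable if block sizes are known, which is why sizes should vary and stay concealed from the practitioners.

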### Intervention

All participants will receive three interventions at the Outpatient Rehabilitation Service of the University Hospital of Brasília (room F49, blue hall), respecting a 7-days washout interval and the same appointment time, which may be scheduled between 8 and 11 a.m.

#### CV4 technique

The participant will be in supine position during the whole procedure. The practitioner sits behind the participant’s head, contacts participant’s lateral protuberances of the squama occipitalis (medially to the occipitomastoid suture) with the thenar eminence of both hands. When the practitioner feels the PRM (a pulsating rhythm caused by liquor production and reabsorption), the flexion phase will be resisted and the extension phase exaggerated. The compressive force is held until the PRM stops (event known as ‘Still point’) [23] (10) (9). The compression will be held until the practitioner feels PRM gradual return; the compression will be slowly diminished, and then, the practitioner remove the hands from the occipital bone, laying the participant’s head on the table. Figure 2 shows the maneuver.

**Fig. 2 Fig2:**
[figure not shown]
Picture of the CV4 technique

The flexion phase of the occipital bone comprises the perception of a centrifugal motion of the squama occipitalis and the flattening of its convexity. The extension phase comprises a centripetal motion of the squama occipitalis and an increase of its convexity. Thus, the practitioner intends to exaggerate the convexity of the squama occipitalis.

The CV4 technique will be performed by an osteopath D.O. - member of the Brazilian Register of Osteopaths.

#### CV4 sham

The participant will be in supine position and the practitioner will be seated behind the participant’s head. The practitioner places the fingers (2nd to 5th) under the occipital bone, touching only the squama occipitalis (Fig. 3). The practitioner will hold this position for the same time the CV4 duration, and after this period the participant’s head will be placed on the table.

**Fig. 3 Fig3:**
[figure not shown]
Picture of the sham technique

The CV4 sham will be performed by a registered physiotherapist ([name]).

#### Control

The participants will be in supine position for the same time the CV4 duration without any visual or verbal contact. A third researcher (a 5th-year osteopathic medicine student) will conduct this phase ([name]).

### Measurements

#### Primary outcome measurement

The mean change in peak alpha frequency (PAF) will be the primary outcome measure to assess the effects of CV4 technique on nonspecific chronic low back pain. PAF is a measure derived from EEG analysis, and it is defined by two parameters: (1) its occurrence on the frequency axis; and 2) its amplitude on the power density axis. The participants assessment (EEG) and the results statistical analysis will conducted by a blinded researcher ([name]).

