#### EEG recording and analysis

The EEG record will be done before and immediately after each protocol section.

EEG bipolar data will be collected from 26 scalp electrodes (Brain Wave II EEG, Inc., São Paulo, São Paulo) placed according to the International 10–20 system (Fp1, Fp2, F7, F3, Fz, F4, F8, FC3, Fcz, FC4, T3, C3, Cz, C4, T4, CP3, Cpz, CP4, T5, P3, Pz, P4, T6, O1, Oz, O2) [24, 25]. This system aims to standardize the electrodes arrangement in specific areas of the scalp surface regardless the size of the skull (Fig. 4). Electrooculogram data will be recorded from electrodes placed above and below the left eye orbit and at the lateral canthus of both eyes.

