**Fig. 4 Fig4:**
[figure not shown]
International 10–20 system [28]

The EEG will be recorded with the eyes closed and opened, and each recording will last 2 min. During the exam, the participants will be in seated position (16). The participants will be given only two verbal commands: to open and close their eyes.

A computerized Fourier analysis of the EEG waves will be made, using the Brain Wave Analyzer Software. The signal will be sampled at 500Hz rate, and filtered with a 1–50 Hz band-pass filter. The signal will be filtered to display alpha frequency (8–13 Hz). Electrode impedance will be kept below 5KΩ, and the ground electrode placed at the Fpz location.

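### Two primary EEG parameters are each tested at 0.05 with no rule linking them, so the error rate is about 10% rather than 5% if either one counts as success

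*Protocol article*

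**What the plan says.** Two places in the protocol article define the primary outcome.

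- Abstract, Methods/Design: power amplitude is listed first, and then "frequencies of the dominant peak in the alpha band will be the primary outcome measures of the study". The wording is plural, so there are two measures.
- Measurements, Primary outcome measurement: "The mean change in peak alpha frequency (PAF) will be the primary outcome measure". This is singular. The text then adds that "it is defined by two parameters: (1) its occurrence on the frequency axis; and 2) its amplitude on the power density axis".

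The section on baseline and outcome data sets the testing rule. A 3 × 2 mixed-effects model (condition by time) is applied "to repeated data measures for each continuous outcome variable", and the 0.05 level "will be considered to all variables". The one multiplicity step is that, after a significant analysis of variance, "a post-hoc test (Bonferroni test) will be used to separate the differences between groups before and after the intervention period".

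The Sample size section works from one two-sided type I error of 5% and 80% power, and arrives at 81 participants.

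On the recordings, the EEG section says "EEG bipolar data will be collected from 26 scalp electrodes" and "The EEG will be recorded with the eyes closed and opened, and each recording will last 2 min". It does not say which eye state, or which electrode or average of electrodes, supplies the value for the primary test.

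**The concern.** A peak's position in Hz and its height on the power axis are two variables. They cannot form one mean change without a combining rule, and none is given. Under the stated testing rule each would get its own model and its own 0.05.

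The hypothesis, in the Abstract and the Background, is only that PAF will be modulated. It gives no direction and does not ask that both parameters move. A significant result on either could therefore be reported as the primary finding. The Bonferroni step does not prevent this, because it works among the three conditions within one variable and not across the two variables.

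What is at stake is the 5% error rate on which the trial was sized. The Discussion says that positive outcomes would support using the technique in a health service, so a doubled false-positive rate on the primary question would matter.

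**Working it through.** **Inputs.** From the article: two parameters; 0.05 for every variable; one two-sided 5% type I error, 80% power, three groups, an effect size of 20% and 81 participants. The article gives no correlation between the two parameters, so values of 0, 0.3 and 0.5 are assumed. One test is counted per parameter.

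**Step 1: the plan's own figure.** Read the 20% as Cohen's f = 0.20 in a fixed-effects two-way ANOVA with 2 numerator degrees of freedom. Power comes from the noncentral F distribution with noncentrality λ = f² × N, where N is the number of observations.

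- 80% power at 0.05 needs N = 244, and 244 / 3 = 81.3 per condition.
- With 81 participants in all three conditions, N = 3 × 81 = 243, λ = 0.04 × 243 = 9.72, and power is 79.8%.

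This reproduces 81, at one undivided level of 0.05. The reading is an assumption. A repeated-measures interaction with correlation 0.5 would give 66 instead.

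**Step 2: familywise error if either parameter suffices.**

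- Independent tests: 1 − (1 − 0.05)² = 1 − 0.9025 = 9.75%.
- Upper bound under any dependence: 0.05 + 0.05 = 10%.
- Correlated tests, simulated with 40,000 replicates of 2-df tests: about 9.5% at correlation 0.3 and 9.0% at 0.5.

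Moderate correlation hardly lowers the rate.

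**Step 3: familywise error if both are required.** With no effect on at least one parameter, a false claim needs a false positive on that parameter, so the rate is at most 5%.

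**Step 4: what each repair costs.**

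- Fixed sequence: the first parameter is tested at 0.05, and the second at 0.05 only if the first is significant. Familywise error is at most 5%. The first test keeps the power of Step 1, so 81 stands.
- Bonferroni at 0.025 each: familywise error is 1 − 0.975² = 4.94% if independent and at most 5% in any case. On the basis of Step 1, power per parameter at N = 243 falls from 79.8% to 71.0%. Restoring 80% needs N = 292, and 292 / 3 = 97.3, so 98 participants.
- The loss depends on the sizing basis. With the repeated-measures interaction at correlation 0.5, power at 81 would go from 89.5% to 83.2%.

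**The case against.** Three objections deserve an answer.

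**The inflation is conditional.** No sentence says that one significant parameter is enough. The Measurements section and the Discussion both speak of a single outcome, the mean change in PAF. If both parameters had to be significant, there would be no inflation. This stands, and it is why the size is given as conditional. It does not remove the problem, because no sentence requires both, and the Abstract lists the two as separate outcome measures.

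**A condensed article may leave detail to a fuller plan.** This is right for the choice of electrode and eye state. It does not cover the one-versus-two conflict or the 0.05 rule for all variables, because the article states both.

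**The error rate might seem far worse than 10%.** A reader might multiply 26 electrodes, two eye states and two parameters into 26 × 2 × 2 = 104 tests and infer that a false positive is almost certain. The article does not support this. It says that these data are recorded, not that each electrode or eye state is tested, and it calls none of them an outcome variable. Averaging, or preselecting a site and state, would remove that part entirely. Testing several separately would raise the rate, but nothing says this will be done.

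**Conclusion.** The point holds in a limited form. The article contradicts itself on whether there are one or two primary outcomes, and its stated testing rule does not protect the single 5% error used for sizing. If either parameter counts as success, the familywise error is 9.75% under independence, about 9.0–9.5% at assumed correlations of 0.3–0.5, and never above 10%. That is roughly double the nominal rate. If both are required, it is at most 5%.

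The 10% bound needs no assumption about correlation. It assumes only one test per parameter and that either one is sufficient. The power figures for Bonferroni rest on reading the 20% as f = 0.20 and on treating the 243 observations as the sizing does. The open choice of eye state and electrode summary adds a possible further inflation, but not an established one.

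**What to change.** Before any results are seen, make the Abstract and the Measurements section agree. Name one parameter as primary, and test the other in fixed sequence at two-sided 5%. This keeps the 5% error and the 81 participants and costs only wording. The drawback is that the second parameter is confirmatory only if the first is significant.

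The order is the sponsor's to choose, and the evidence behind it should be weighed. The aim and hypothesis are worded in terms of peak frequency. But the Background describes the pilot study used for sizing as showing a rise in absolute alpha power, in healthy participants. If frequency goes first, the sizing has no described pilot result for that variable.

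If both parameters are to have equal standing, use Holm or Bonferroni across the two and restate the power. It is about 71% per parameter at the 0.025 level with 81 participants, or 98 participants for 80%, on the sizing basis shown above. Holm does better than this only for a parameter tested after the other has already been significant.

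In the same sentence, state the one eye state and the one spatial summary that supply the primary value, and label the other eye state and single-electrode results as exploratory. If a separate analysis plan already fixes these choices, it is enough to bring the article's wording into line with it.
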